# Combining motivational and volitional strategies to promote unsupervised walking in patients with fibromyalgia: study protocol for a randomized controlled trial

**DOI:** 10.1186/1745-6215-15-120

**Published:** 2014-04-11

**Keywords:** Fibromyalgia, Implementation intention, Intervention, Theory of planned behavior, Walking

## Abstract

**Background:**

Fibromyalgia patients are often advised to engage in regular low- to moderate-intensity physical exercise. The need of fibromyalgia patients to walk has been stressed in previous research. Behavioral self-regulation theories suggest that a combination of motivational aspects (to develop or strengthen a behavioral intention: Theory of Planned Behavior) and volitional aspects (engagement of intention in behavior: implementation intentions) is more effective than a single intervention. In this paper, we describe a protocol for identifying the motivational processes (using the Theory of Planned Behavior) involved in the practice of walking (phase I) and for studying the efficacy of an intervention that combines motivational and volitional contents to enhance the acquisition and continuation of this exercise behavior (phase II). The paper also shows the characteristics of eligible individuals (women who do not walk) and ineligible populations (women who walk or do not walk because of comorbidity without medical recommendation to walk). Both groups consist of members of any of four patients’ associations in Spain who are between 18 and 70 years of age and meet the London Fibromyalgia Epidemiology Study Screening Questionnaire criteria for fibromyalgia. Furthermore, using this study protocol, we will explore the characteristics of participants (eligible women who agreed to participate in the study) and nonparticipants (eligible women who refused to participate).

**Methods/design:**

Two studies will be conducted: Phase I will be a cross-sectional study, and phase II will be a triple-blind, randomized longitudinal study with two treatment groups and one active control group. The questionnaires were sent to a total of 2,227 members of four patients’ associations in Spain. A total of 920 participants with fibromyalgia returned the questionnaires, and 582 were ultimately selected to participate.

**Discussion:**

The first data gathered have allowed us to identify the characteristics of the study population and they support the appropriateness of the inclusion criteria.. When the study is complete, the results will enable us to establish whether this kind of intervention can be used as a self-regulation tool for increasing and maintaining walking as unsupervised physical exercise of low to moderate intensity in fibromyalgia patients.

**Trial registration:**

Trial registration number:
ISRCTN68584893

## Background

Fibromyalgia (FM) is a complex chronic condition characterized by widespread musculoskeletal pain, fatigue, sleeping problems and other symptoms with no well-established etiology. Physical exercise is a component of effective treatment
[1], and aerobic exercise in particular has been shown to lead to improvements in various health outcomes
[2-7]. To the best of our knowledge, most studies conducted to date have included supervised physical exercise programs, which are often associated with low patient adherence
[8-12]. In fact, one of the main challenges in FM treatment is achieving long-term adherence to maintain the positive effects of physical exercise on patients’ health
[10,13]. Some authors have suggested that adherence represents a main issue and should be a mandatory focus in studies of physical exercise
[6]. Walking is a low- to moderate-intensity exercise which has been shown to have positive effects on FM patients’ health status
[4,14,15] and is a well-established aerobic activity for these patients
[10]. It is also a simple recommendation that promotes patients’ self-management.

Any behavior, such as walking, is more likely to be practiced if people are motivated and develop strategies to engage in it. In the general population, combining motivational and volitional interventions to increase physical exercise or walking are more effective than initiating and promoting each of them separately
[16-20]. Motivational intervention encourages individuals to form an intention, and volitional intervention encourages them to form a plan stating when, where and how they will carry out their intention (implementation intentions). In FM patients, however, this combination has not been tested. It is important to examine this issue in this population because the presence of symptoms such as pain and fatigue, which are associated with FM, could affect walking behavior. Furthermore, these symptoms may influence both motivational and volitional processes for starting and maintaining walking behavior in FM patients, which is not the case in the general population. Recently, Ang *et al*.
[21] applied an intervention using motivational interviewing to increase supervised walking in FM patients. As these authors underlined, this strategy is not based on any specific theory of health behavioral change. In spite of the good results in the short-term, they concluded that motivational interviewing alone is insufficient to increase physical activity in the long term. These results support the importance of using volitional strategies as well as basing the intervention on well-established theories of health behaviors.

The Theory of Planned Behavior (TPB)
[22-24] is a well-established theory in health behavior and has been shown to have predictive power regarding walking and physical exercise
[25,26]. In FM patients, TPB constructs (see the “Interventions” subsection below) explained 32% of the variance in the intention to exercise
[27]. However, a strong behavioral intention is necessary, but not sufficient, to implement action. The implementation intentions are a theoretical proposal that focuses on the gap between intention and action
[28]. Implementation intentions are specific plans that enhance the transition of goal intentions into actions. Motivation is the starting point for behavioral change and volitional strategies, based on implementation intentions, to increase the likelihood of this change
[18]. Once the behavior is started, the processes associated with implementation intentions (automatic activation of the behavior when environmental cues are present) are expected to promote maintenance of the behavior because it neither consumes cognitive resources nor produces ego depletion as other self-regulation processes do. Moreover, we expect that the benefits on health status associated with walking behavior will also promote its maintenance in the long term. In other populations and behaviors, the implementation intentions approach has produced better long-term behavioral change
[29]. Thus, we expect to find similar effects in our FM population.

Applying both theories to promote behavioral change in FM is expected to allow us to cover two basic processes: (1) the adoption or strengthening of behavioral intentions (motivational process) and (2) their effects on behaviors (volitional or postmotivational process). In the FM context, some special features, such as pain, health status impact and fear of movement, should also be considered
[30]. These factors can influence both the intention to exercise and the exercise behavior itself. In fact, some factors have been observed to be barriers to walking ([name], unpublished manuscript). Not taking these factors into account has been considered a limitation of previous studies
[21].

To increase walking as unsupervised physical exercise, it is important to test whether an intervention which includes motivational strategies (intentions) and volitional strategies (implementation intentions) will be effective. This paper describes the two phases of a protocol. In phase I, we will identify the motivational processes involved in intentions of performing a recommended walking pattern in FM patients, using the TPB and considering the above-mentioned specific FM factors. In phase II, to establish the efficacy of an intervention that combines both motivational processes (based on the results of phase I) and volitional processes to enhance the short-, medium- and long-term adherence to a walking program.

This paper also describes the characteristics of eligible populations (women belonging to FM associations, between 18 and 70 years of age, meeting the London Fibromyalgia Epidemiology Study Screening Questionnaire criteria (London-4) (see http://www.aafplearninglink.org/Resources/Upload/File/AAFP-10-106-London%20Screening-09-07-10.pdf) for FM and unable to walk) and noneligible populations (same characteristics mentioned above, but either able to walk or do not walk because of comorbidity without medical recommendation for walking). This aim is needed to test the similarities between both populations in order to ensure the external validity of the study. We will also explore the characteristics of participants (women from the eligible population who agreed to participate in the study) and nonparticipants (women who refused to participate).

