#### Phase I

Descriptive analyses have been performed. The sociodemographic characteristics, symptoms, walking and physical activity of eligible and noneligible populations have been compared by conducting χ^2^ tests, *t*-tests, analysis of variance and median nonparametric tests, depending on the characteristics of the variables (Table 
4). These comparisons were conducted to ensure that both samples differ only with regard to the inclusion criteria of the study. The same analyses were performed to compare participants with individuals who refused to participate and nonresponders (that is, not contacted or not available at the time of measurement) (Table 
5).

**Table 4 T4:** **Descriptive statistics in eligible and noneligible populations**^
**a**
^

**Variables**	**Noneligible**					**Eligible**				
	**Mean**	**(95% CI)**	**SD**	**Median**	**(95% CI)**	**Mean**	**(95% CI)**	**SD**	**Median**	**(95% CI)**
Age (years)	53.51	(52.59 to 54.42)	8.52	54.24		52.14	(51.41 to 52.87)	8.96	52.91	
Pain intensity	6.63	(6.43 to 6.83)	1.82	6.62		6.73	(6.59 to 6.87)	1.70	6.75	
Fatigue	8.01	(7.79 to 8.23)	2.01	8.00		8.20	(8.36 to 8.39)	1.96	9.00	
Fatigue upon waking	7.99	(7.74 to 8.25)	2.37	9.00		8.17	(8.00 to 8.25)	2.20	9.00	
Fatigue impact perception	6.78	(6.48 to 7.08)	2.77	7.00		7.01	(6.78 to 7.23)	2.72	7.00	
Cognitive problems	6.77	(6.48 to 7.05)	2.62	7.00		7.00	(6.78 to 7.21)	2.66	8.00	
Sleeping disorder impact perception	7.07	(6.75 to 7.38)	2.94	8.00		7.02	(6.70 to 7.26)	2.95	8.00	
Cognitive problems impact perception	6.30	(6.00 to 6.61)	2.83	7.00		6.57	(6.34 to 6.80)	2.83	7.00	
IPAQ-Sitting, mi/wk				240.5	(240.5 to 300.5)				300.5	(240.5 to 300.5)
IPAQ-Walking, min/wk				300.5	(245.5 to 350.5)				180.5	(140.5 to 180.5)
IPAQ-Moderate activities, min/wk				0.5	(0.5 to 60.5)				0.5	(0.5 to 0.5)
IPAQ-Vigorous activities, min/wk				0.5	(0.5 to 0.5)				0.5	(0.5 to 0.5)
IPAQ-Total activities, min/wk				383.5	(300.5 to 420.5)				180.5	(150.5 to 210.5)
	** *n* **	**(%)**				** *n* **	**(%)**			
Education level										
Literate	42	(12.5)				67	(11.5)			
Primary	138	(40.9)				261	(44.8)			
Secondary	106	(31.5)				163	(28.0)			
University	51	(15.1)				91	(15.6)			
Employment status										
Working	88	(26.3)				177	(30.5)			
Unemployed	63	(18.8)				118	(20.4)			
Retired	26	(7.8)				38	(6.6)			
Retired (pain)	39	(11.6)				59	(10.2)			
Sick leave	32	(9.6)				50	(8.6)			
Housewife	87	(26.0)				138	(23.8)			

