No significant differences were found between the noneligible population (*n* = 338) and the eligible population (*n* = 582) regarding the distribution of the patients drawn from the different FM associations (χ^2^ = 2,670, *P* = 0.445, df = 3. With regard to sociodemographic variables, we found significant differences only for age between the eligible and the noneligible populations (*t* = 2.264, *P* = 0.024, df = 914, mean difference = 1.37, 95% CI = 0.18 to 2.55). This difference was not found, however, when we considered the FM associations in the analysis (eligible group by FM association: F = 1.928, *P* = 0.124; noneligible group by FM association: F = 2.403, *P* = 0.067). No significant differences were found between groups for either education level (χ^2^ = 1.810, *P* = 0.613, df = 3) or employment status (χ^2^ = 5.912, *P* = 0.436, df = 6). Groups were also similar in pain intensity perception (*t* = -0.833, *P* = 0.415, df = 913), fatigue (*t* = -1.38, *P* = 0.167, df = 909), fatigue upon waking (*t* = -1.16, *P* = 0.245, df = 910), impact perception of fatigue (*t* = -1.21, *P* = 0.226, df = 909), cognitive problems (*t* = -1.27, *P* = 0.205, df = 910), impact perception of cognitive problems (*t* = -1.37, *P* = 0.173, df = 908) and impact perception of sleeping disorders (*t* = 0.25, *P* = 0.806, df = 911). The last six variables were included in the mailed questionnaire to identify the study population. All of them were calculated for the previous week and were measured using an 11-point numerical rating scale (from 0 = nothing at all to 10 = totally). In relation to IPAQ-S variables, median total activity, walking and moderate-intensity activities were different (*P* ≤ 0.01) and similar in vigorous activities (*P* = 0.296) and sitting (*P* = 0.442) (Table 
4).

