TPB is the selected theoretical model for the design of the motivational intervention. It has allowed us to identify the modal salient beliefs (behavioral, normative and control) in a previous elicitation study with a sample of the study population ([name], unpublished manuscript). As soon as the predictors of the behavioral intention are assessed in phase I, we will address the specific beliefs of FM participants, which should be modified or strengthened in the motivational intervention. By adding to these intervention implementation intentions, we expect to enhance the selected walking behaviors and to raise adherence. Both strategies have been recommended elsewhere
[5]. Furthermore, using implementation intentions encourages each participant to carry out their own action plans (based on the established minimum), taking into account their personal circumstances.

The initial data have allowed us to identify the characteristics of the study population. In addition, the preliminary results have shown differences between members of the FM population who meet the inclusion criteria in this study (eligible population) and those who do not (noneligible) in total, moderate and walking activities. These results support the appropriateness of these criteria with regard to walking patterns. The activities and demographic characteristics of the participants who refused to participate, as well as the nonresponders from the eligible population, were similar to those of the participants. Although participants were different in regard to moderate intensity activities, the median values were the same and only a slightly higher percentage of FM participants took part in moderate activity as compared to nonparticipants. These results also support the representativeness of the study sample. We are aware of the difficulties of the research because the targeted population is sedentary. However, the effect of exercise interventions has been substantial in this type of patient.

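### The eligible-versus-noneligible age difference is set aside with tests that do not address it, and Table 4's pooled noneligible column shows only average similarity

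*Protocol article*

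**What the plan says.** The abstract and the Background both define the noneligible group by two routes. In the Background it is women who are "either able to walk or do not walk because of comorbidity without medical recommendation for walking"; in the abstract, "women who walk or do not walk because of comorbidity without medical recommendation to walk". The purpose of comparing them with the eligible women is given twice. The Background says: "This aim is needed to test the similarities between both populations in order to ensure the external validity of the study". The Phase I part of the statistical analysis section says: "These comparisons were conducted to ensure that both samples differ only with regard to the inclusion criteria of the study".

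Table 4 shows one noneligible column (338 women) beside one eligible column (582 women). The Phase I text reports a significant age difference (t = 2.264, P = 0.024, "mean difference = 1.37, 95% CI = 0.18 to 2.55") and continues: "This difference was not found, however, when we considered the FM associations in the analysis". The support offered is an F of 1.928 (P = 0.124) for the eligible group by association and an F of 2.403 (P = 0.067) for the noneligible group by association. Pain, fatigue, cognitive and sleep scores are described as similar on nonsignificant t tests.

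The Discussion points to the differences in total, moderate and walking activity and concludes: "These results support the appropriateness of these criteria with regard to walking patterns".

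**The concern.** There are two separate points.

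**Age.** A significant between-group difference is declared absent on the strength of tests that, as labelled, look inside each group. Whether mean age varies across four associations among eligible women, and again among noneligible women, says nothing about whether the two groups differ. A reader would take away that the difference was explained by association. The reported tests do not show that.

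**Pooling.** A woman is noneligible either because she already walks or because a comorbidity stops her and no doctor has advised walking. The aim of showing that the samples differ only on the inclusion criteria has to hold for each route, because each route is an inclusion criterion. One pooled mean cannot show that. The Background itself says that symptoms such as pain and fatigue could affect walking, so it is reasonable to ask whether the two kinds of excluded women differ from the eligible women in different directions.

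At stake is what the stage 1 comparison may be said to show about the population the sample represents.

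**Working it through.** **Age: reproducing the reported result.** Inputs from Table 4: noneligible mean 53.51, SD 8.52, n = 338; eligible mean 52.14, SD 8.96, n = 582. Full group sizes are used; the reported df of 914 implies that a few ages are missing.

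- Difference: 53.51 − 52.14 = 1.37 years.
- Pooled SD: √[(337 × 8.52² + 581 × 8.96²) / 918] = 8.80.
- Standard error: 8.80 × √(1/338 + 1/582) = 0.602.
- t = 1.37 / 0.602 = 2.28, P = 0.023, 95% CI 0.19 to 2.55. The article gives 2.264, 0.024 and 0.18 to 2.55, so it is reproduced within rounding and missing values.
- Standardized difference: 1.37 / 8.80 = 0.16.

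**Age: what the two F tests are.** With four associations, a within-group test has 3 numerator df and n − 4 denominator df.

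- Eligible: F(3, 578) = 1.928 gives P = 0.124 (printed 0.124).
- Noneligible: F(3, 334) = 2.403 gives P = 0.067 (printed 0.067). On the whole sample, with about 908 residual df, the same F would give 0.066.

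Labels and P values both fit age-by-association tests inside each group. Neither contains an eligibility term.

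**Pooling: could subgroup differences be hidden?** Pain in Table 4 is 6.63 (SD 1.82) for noneligible and 6.73 (SD 1.70) for eligible women. The difference is −0.10, pooled SD 1.745, standard error 0.119, t = −0.84 (article −0.833), 95% CI −0.33 to 0.13.

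Let q be the share of the 338 excluded for comorbidity, and D the gap in mean pain between the two noneligible subgroups. Then:

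- pooled difference = (1 − q) × d(walkers) + q × d(comorbid);
- pooled variance = within-subgroup variance + q(1 − q)D².

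The text does not give q or the subgroup means. The illustration assumes a within-subgroup SD of 1.70 and keeps the pooled difference of −0.10 and pooled SD of 1.82. Then D = √[(1.82² − 1.70²) / (q(1 − q))] = √[0.4224 / (q(1 − q))], d(walkers) = −0.10 − qD and d(comorbid) = −0.10 + (1 − q)D.

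| q (assumed) | D | Walkers vs eligible (t) | Comorbid vs eligible (t) |
|---|---|---|---|
| 0.1 | 2.17 | −0.32 (−2.6) | +1.85 (6.2) |
| 0.2 | 1.62 | −0.42 (−3.4) | +1.20 (5.5) |
| 0.3 | 1.42 | −0.53 (−4.0) | +0.89 (4.9) |
| 0.5 | 1.30 | −0.75 (−5.0) | +0.55 (3.7) |

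Subgroup differences of this size are arithmetically compatible with a pooled t of −0.84. The table shows what Table 4 cannot exclude for pain. It does not estimate what happened.

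**The case against.** **The pooled group may be the right comparator.** If the question is whether eligible women resemble, on average, the rest of the 920, the whole complement of 338 is what should be compared, and cancellation does that average no harm. This stands. It limits what the comparison shows but does not make it worthless.

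**Cancellation is not shown.** The subgroup shifts above follow from an assumed split and an assumed within-subgroup SD. Opposed subgroups would tend to widen the noneligible SD, and Table 4 shows no consistent widening: cognitive problems 2.62 against 2.66, sleep impact 2.94 against 2.95, cognitive impact 2.83 against 2.83, with modest widening for pain (1.82 against 1.70) and fatigue on waking (2.37 against 2.20). Subgroup counts may be in the recruitment flowchart, which is not visible in the text, although counts alone would not give subgroup means. All of this stands.

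**Little is concluded from the null tests.** A reader might infer that Table 4 is used to claim external validity and cannot support it. The documents do not bear that out. External validity and differing only on the criteria are stated as purposes. The Discussion's conclusion from Table 4 concerns walking patterns and rests on activity differences such as median walking of 300.5 against 180.5 minutes per week. Representativeness is argued after the comparison of participants with nonparticipants in Table 5. Nor does the article extend its results to walkers or to women with limiting comorbidity.

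**The age difference is disclosed and small.** True: its CI is printed and it is about 0.16 SD. That does not rescue the sentence saying it was not found.

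**Conclusion.** The point on age holds on the page. The article says a difference of 1.37 years (95% CI 0.18 to 2.55) was not found after considering associations, and the tests cited do not examine that difference. This rests on reading the F tests as within-group, which their labels and P values both support. The difference is small, but it stands as reported.

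The point on pooling holds in a limited form. Table 4 shows average similarity to the rest of the 920-woman reference population, with pain as an example (−0.10, 95% CI −0.33 to 0.13). It does not establish similarity to walkers or to comorbid non-walkers separately. Opposite differences are possible over an assumed comorbid share of 10% to 50%, but they are not demonstrated.

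The Discussion's conclusion about walking patterns is untouched, as is the randomized phase II comparison. The correction is still worth making because it changes what the stage 1 comparison can be said to show.

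**What to change.** 1. In the Phase I results, replace the two F tests with one linear model of age on eligibility and association, and report the adjusted eligible-versus-noneligible difference with its 95% CI. Alternatively, delete the sentence and state that the age difference of 1.37 years (about 0.16 SD) stands.
2. In Table 4, split the noneligible column into women who already walk and women excluded for comorbidity, give the size of each, and compare each with the eligible group by mean difference and 95% CI. The pooled column can stay as the comparison with the rest of the reference population.
3. In the Background aims and the Phase I analysis text, limit the wording on external validity and on differing only by the inclusion criteria to average similarity, or to whichever subgroup the intervals support.

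The cost is a re-run of a descriptive table, provided the reason for exclusion was kept for each woman, as applying the criteria implies. The one downside is wider intervals in the smaller subgroup. Nothing in the phase II design or analysis needs to change.
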